## Abstract

•Evidence for best shock energy to treat out-of-hospital cardiac arrest is lacking.•POSED is a feasibility study for a future trial intended to close the evidence gap.•90 patients will be recruited within a single NHS Ambulance Service.•Feasibility will be tested by comparing numbers of eligible with recruited patients.•We will select best outcomes for a trial based on clinical relevance, reliability and ease of recording.

Evidence for best shock energy to treat out-of-hospital cardiac arrest is lacking.

POSED is a feasibility study for a future trial intended to close the evidence gap.

90 patients will be recruited within a single NHS Ambulance Service.

Feasibility will be tested by comparing numbers of eligible with recruited patients.

We will select best outcomes for a trial based on clinical relevance, reliability and ease of recording.

## Introduction

### Background and rationale

Globally between 30 and 97 patients per 100,000 population receive treatment by Emergency Medical Services for cardiac arrest each year.^1^ Defibrillation is the mainstay treatment for patients displaying ventricular fibrillation or pulseless ventricular tachycardia, but even following a witnessed collapse, only 10–33% survive with favourable neurological outcome.^1^ Chances of survival decrease with increasing duration of ventricular fibrillation.^2^ Amongst witnessed cases, the chance of survival to 30 days decreases with each shock (odds ratio (OR) 0.9; 95% Confidence Interval (CI) 0.88–0.92).^3^ An optimal shock energy strategy can shorten the resuscitation duration. This is important as longer resuscitation durations (31 minutes versus 5 minutes) are associated with a significantly lower chance of survival with a favourable neurological outcome (adjusted OR 0.04; 95% CI 0.03–0.05).^4^

### First shock success

Although several studies report first shock success, none has provided sufficient strength of evidence on which to base treatment recommendations. As such, current guidelines permit the use of any defibrillation energy level between 120–360 J.^5^ The International Liaison Committee on Resuscitation (ILCOR) has identified defibrillation energy levels as a priority area for research.^6^

A previous systematic review reported no observed difference in first shock success for energy levels between 120 and 200 J.^7^ Eight identified papers reported data from six studies but these compared a variety of waveforms, different measures of shock success and were undertaken at a time when resuscitation protocols recommended 3 stacked shocks and less focus on high-quality CPR. Of studies using 2010 CPR guidelines, with the emphasis on early defibrillation and single shocks separated by high-quality CPR, two report first shock success.^8^, ^9^ The first of these compares manual versus automated delivery of 360 J biphasic truncated exponential (BTE) waveform shocks, where fibrillation was terminated in 80.7–84.3% of cases.^8^ The second paper does not report energies and includes two different biphasic waveforms, but does not distinguish between them when reporting outcomes.^9^

### Shock strategy

Should further shocks be required, no strong evidence favours delivery at the same level or escalating the energy.^10^ In the BIPHASIC trial, escalating high-energy protocol was more successful than fixed low-energy protocol at both terminating fibrillation (81.8% vs 71.8%) and restoring an organised rhythm (36% vs 25.7%).^11^ However, a stacked shocks regime was employed, and the study was underpowered to detect a difference in survival. Our recent systematic review identified a recent post-hoc analysis of the CIRC trial, comparing manual and mechanical chest compression delivery, which explored the effect of shock strategy.^12^ No difference in long-term survival was detected between patients receiving escalating energy shocks (200–300–360 J) and those receiving fixed high-energy shocks (360–360–360 J) (unadjusted risk ratio 0.99, 95% CI 0.73, 1.23).^13^ However, no strong conclusions can be drawn due to the post-hoc non-randomised nature of the analysis.

There is a clear need for further research to determine the optimal shock energy strategies for first and subsequent shocks, and their effects on clinical outcomes. However, whether such a trial is feasible is currently unknown. Therefore, this study aims to determine: *Is it feasible to conduct a randomised, pragmatic clinical effectiveness trial in UK ambulance services to identify the optimal energy for defibrillation?* The primary objective of this study is to establish whether it is feasible to conduct a large-scale definitive trial based on the number of eligible patients and the number recruited. The secondary objectives are (1) to measure the rate of adherence to the allocated treatment, (2) identify the best outcome measures in terms of clinical relevance, ease and reliability of recording. We present the study according to SPIRIT guidelines (Appendix A1).^14^

## Methods

### Protocol

The full protocol and statistical analysis plan and any future updates are available on the trial website: https://warwick.ac.uk/fac/sci/med/research/ctu/trials/posed/.

The protocol was developed in accordance with the principles of the Declaration of Helsinki and Good Clinical Practice (GCP) and guidance from the Standard Protocol Items: Recommendations for Intervention Trials (SPIRIT).^14^ Core study information is presented in Appendix A2. The study is conducted and managed by the Warwick Clinical Trials Unit (WCTU) and sponsored by University of Warwick, Research & Impact Services, [name].

### Study design

POSED is a pragmatic, allocation-concealed, open label, cluster randomised (by defibrillator) controlled feasibility study with a 1:1:1 allocation ratio.

### Study setting

Recruitment to this single-site study will be led by South Central Ambulance Service, an NHS ambulance service in the south of England. The trial opened to recruitment on 22 March 2022.

### Eligibility criteria

Patients will be included if they sustain an OHCA attended by a crew carrying a study defibrillator, resuscitation is attempted and a shock delivered. Patients known or suspected to be under 18 years old are excluded.

### Study interventions

Defibrillators are routinely pre-programmed to deliver consistent 1st, 2nd and subsequent shock energies within an ambulance service. These pre-programmed energies are the default settings whether used in automatic or manual mode. In this study, Zoll X-series defibrillators (rectilinear biphasic waveform) have been randomised to deliver one of three shock strategies as described in Table 1. Strategies are pre-programmed by the researcher to optimise protocol adherence and remain default settings in both automatic and manual mode. Protocol adherence will be monitored via the study database; when data from defibrillators is entered, any discrepancy between allocated and delivered energy will automatically raise an alert on the database.

**Table 1 t0005:** Energy levels of treatment groups (J = joules).

Group	First shock	Second shock	Subsequent shocks	Strategy	Intervention/Comparator
1	120 J	150 J	200 J	Escalating	Comparator
2	150 J	200 J	200 J	Escalating	Intervention
3	200 J	200 J	200 J	Fixed	Intervention

The treatment groups represent three variations in current UK practice. Group 1, the most commonly used strategy, delivers shock energies according to manufacturer’s current guidance. Group 2 and 3 interventions provide higher first shock energies, escalating or maintaining at the highest energy for the second and subsequent shocks.

The treatment allocation determines the energy levels of the first three sequential shocks. Should a return of spontaneous circulation (ROSC) be observed and then refibrillation occur, the patient will receive the next sequential allocated energy level. If the defibrillator is changed during a patient care episode, normal site policy will apply regarding shock energy escalation (i.e. second and subsequent shocks to be delivered at 200 J).

Clinical management of patients will adhere to the 2021 Resuscitation Council UK Advanced Life Support Guidelines.^5^ The study protocol does not mandate or prohibit any specific concomitant care. Study treatment ceases either when out-of-hospital resuscitation efforts are discontinued or upon handover of care to the hospital team who will deliver their usual care.

### Outcome measures

#### Primary outcome measure

The primary feasibility outcome is the proportion of eligible patients who receive the randomised intervention.

#### Secondary outcome measures

The secondary feasibility outcomes are**:**•Treatment adherence rate.•Data completeness of the following clinical outcomes:oReturn Of Organised Rhythm (ROOR) 2 min post shockoResulting rhythm (VF/pulseless VT/pulseless electrical activity (PEA)/asystole) 2 min post shockoRe-arrest rate (re-fibrillation)oSurvived event (ROSC at hospital handover)oSurvived to 30 days and hospital dischargeoNeurological function (mRS score) at 30 days and hospital discharge

In addition to the outcomes described above, the study will also assess the acceptability of approach to informing relatives of non-survivors.

We will also report process outcomes including CPR metrics and resuscitation treatments (see Appendix A3). A schedule of assessments is provided in Table 2.

**Table 2 t0010:** Study outcome assessment time points, POSED, Prehospital Optimal Shock Energy for Defibrillation.

	Cardiac arrest	Hospital	Day 30
Inclusion/exclusion criteria	✓	✗	✗
Cardiac arrest data	✓	✗	✗
Patient identifiers	✓	✓	✗
Adverse event reportingo	✓	✓	✗
National data opt-out check	✓		✗
Survival checks	✓	✓	✗
Survival status	✓	✓	✓
Hospital stay data	✗	✓	✗
Notification of enrolment and invitation to take part in follow up	✗	✓	✗
Informed consent	✗	✓	✗
Neurological outcome (mRS)	✗	✗	

### Patient timeline

Participants are enrolled on receipt of the randomised intervention (i.e., when a shock from a randomised defibrillator is delivered to an adult patient). A time schedule is provided in Appendix A4.

### Sample size

This feasibility study aims to recruit 90 patients, ideally 30 in each arm. This is in keeping with a recommended sample size of at least 50 for feasibility studies,^15^ whilst allowing roughly equal recruitment into each arm. In order to reach target sample size, defibrillators on every vehicle based in the study area (*n* = 36) were randomised and pre-programmed, eliminating the additional task of selecting the intervention energy at the patient’s side.

### Allocation

#### Sequence generation

The unit of randomisation is the defibrillator (cluster), which is allocated to one of the three treatment groups in a 1:1:1 ratio using simple randomisation, stratified by vehicle type (ambulance, response car, team leader vehicle). Ambulance staff are allocated to appropriate vehicles by rota, so in practice will use defibrillators randomised across all three strategies.

#### Allocation concealment mechanism

Randomisation was achieved using the callsigns of the vehicles carrying the defibrillators. The callsign was allocated to one of the treatment groups (1, 2 or 3) ensuring allocation concealment from the ambulance crews.

#### Implementation

The allocation sequence was computer-generated, and the allocations programmed into the defibrillators by the researcher.

### Blinding

At the point of defibrillator charging, ambulance staff will see the pre-set treatment allocation and so will not be blinded. The clinical outcomes assessed following randomisation are largely objective in nature, so bias due to unblinding should not be an issue. However, we will monitor the data to assess any peculiarities which may be suspicious in the data. Due to the clinical nature of cardiac arrest, patients will be blind to treatment allocation. Control room vehicle dispatchers will be unaware of the treatment allocation. Hospital staff treating patients may be blind to the patient’s treatment allocation since the shock energy is not routinely included in the verbal handover. If patients ask what treatment they received, they will be asked not to pass this information to the research paramedic as the modified Rankin Scale (mRS) assessment should be completed blind to the treatment allocation.

### Data collection methods

Eligible patients are identified from Ambulance service Computer Aided Despatch (CAD) data and Electronic Patient Records (ePR). Data downloaded from defibrillators will indicate the treatment received.

Enrolments will be identified by research paramedics via ambulance service electronic systems reports. We will extract patients’ out-of-hospital data and ambulance response data from routinely collected ambulance service records. Patient and event characteristics, Utstein variables, out-of-hospital treatments and initial outcome will be sought from the patient clinical record. Defibrillator data (treatment summary report) can be downloaded from Zoll X-series devices onto USB devices and viewed via Zoll ‘RescueNet™ Code Review’ software (v5.9.0.5).^16^ Rhythm interpretation will be performed by HP and checked by [name]. We will assess mRS using the Rankin Focussed Assessment (RFA) tool which tool has excellent inter-observer reliability (unweighted κ of 0.93 (95% CI, 0.85–1.00)).^17^

Study data shall be entered at site onto electronic Case Report Forms (CRFs) on a secure university-hosted database, accessible only to authorised personnel.

Following enrolment, we will meet patients face to face in hospital where possible or will write to them following discharge if not. We prefer the former approach as it demonstrates the requisite sensitivity and respect and, in our previous experience, promotes participant retention. We will continue to collect and analyse patient data for those in receipt of an intervention which deviated from the protocol. Site shall perform Critical Data Item checks of dates of birth; should we find that a patient under 18 years old has been entered into the study, no further data shall be collected. In both cases, the non-compliance protocol shall be followed.

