### Statistical methods

We will present summary statistics, namely mean, standard deviation, median, interquartile ranges and missingness in the data. Where possible we will also provide 95% confidence intervals.

Baseline and process data will be presented using descriptive statistics; categorical variables will be presented as proportions and continuous variables as medians with ranges stated. We shall report the proportion of patients in each arm (intention-to-treat) with complete data. No formal statistical comparisons of outcomes will be performed as the study is not powered to detect differences between the interventions.

We will report treatment adherence rate in terms of how many patients received the allocated first shock energy and, where applicable, how many received the correct subsequent shock energies. Additionally, we shall conduct sub-group analyses of survival status at hospital handover, discharge and 30 days where the initial rhythm is shockable (VF/pVT) to explore any interaction between sub-groups and treatment arm. Full details can be found in the Statistical Analysis Plan on the study website.

We will assess the feasibility of informing the relatives of non-survivors by recording (1) the proportion of patients where contact details for a relative was identified, (including time taken to identify relatives, source of information and concordance/discordance between sources) (2) proportion of sent letters returned as unknown at that address (3) record the number and nature of enquiries received by the Ambulance service in response to receipt of a letter.

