### Data monitoring

A Study Oversight Committee has been appointed, led by an independent chair, comprising the co-chief investigators, study statistician and two lay representatives. There will be no Data Monitoring Committee since this feasibility study requires no interim analyses and data will be assessed for completeness rather than for efficacy/effectiveness. The Study Management Group, consisting of the project staff and co-investigators involved in the day-to-day running of the study, will meet monthly. Significant issues arising from management meetings will be referred to the Study Oversight Committee or Investigators, as appropriate. Throughout the project, we will continue to collaborate with the local Patient and Public Involvement (PPI) advisory panel.

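### Outcomes are to be chosen partly on reliability of recording, but completeness plus a checked rhythm reading leaves reader agreement for ROOR and resulting rhythm unmeasured

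*Protocol article*

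**What the plan says.** **The criterion.** The second of the secondary objectives (Introduction, Shock strategy) is to "identify the best outcome measures in terms of clinical relevance, ease and reliability of recording". The Abstract repeats it: "We will select best outcomes for a trial based on clinical relevance, reliability and ease of recording". The Discussion again describes the best measures as both easy and reliable to collect.

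**The measure.** Under Secondary outcome measures, the entry covering the clinical outcomes is "Data completeness of the following clinical outcomes". The list includes ROOR and resulting rhythm, both at 2 minutes after the shock. Statistical methods gives the matching analysis: "We shall report the proportion of patients in each arm (intention-to-treat) with complete data". Data monitoring says the same of purpose: "data will be assessed for completeness rather than for efficacy/effectiveness".

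**The reading.** ROOR is determined after the event from the rhythm recorded by the defibrillator, and the Discussion defines it as two QRS complexes less than 5 s apart. Data collection methods states "Rhythm interpretation will be performed by" one team member and that another checks it. The article describes no separate second reading and no agreement statistic for rhythm.

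**Nearby items that do not fill the gap.** The kappa of 0.93 (95% CI 0.85 to 1.00) in Data collection methods is a cited property of the tool used for the modified Rankin Scale (mRS). The 10% check in Data management follows single data entry, so it concerns transcription.

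**The concern.** A feasibility study that selects outcomes on three criteria should produce evidence on each. Reliability has two parts: whether the recording can be obtained dependably, and whether it is classified consistently once obtained. Completeness addresses the first part only. A data set can be fully complete and still be read differently by different people.

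This matters most for ROOR and resulting rhythm, the outcomes closest to the shock, because both depend on someone interpreting a trace. If a checked reading is the only second look, the team will decide whether to carry these outcomes into a large trial without knowing how often two readers would differ. The study already has two readers and the traces, so the information is within reach and would be lost through the order in which the reading is done.

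**Working it through.** **Step 1. The plan's own figure.** The target is 30 in each of 3 arms: 3 × 30 = 90. It reproduces, it is not derived from a precision or power target, and this point does not dispute it.

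**Step 2. Criterion against measure.**

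| Part of objective 2 | Evidence in the article |
|---|---|
| Clinical relevance | Assessable; argued in the Discussion |
| Ease of recording | Assessable from access to downloads and follow-up |
| Reliability: recording obtained | Data completeness |
| Reliability: recording read consistently | None for ROOR or resulting rhythm |

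**Step 3. What a checked reading can show.** Suppose two independent readers would disagree on a fraction d of traces, and a checker who sees the first answer overturns only a fraction f of those. The observed overturn rate is d × f. With equal reader margins and prevalence p:

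- chance agreement: pe = p² + (1 − p)²
- true kappa = (1 − d − pe) / (1 − pe)
- apparent kappa = (1 − d·f − pe) / (1 − pe)

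Take p = 0.36 as an illustration. It is the organised-rhythm rate for the escalating arm of the earlier trial cited under Shock strategy. Then pe = 0.1296 + 0.4096 = 0.5392 and 1 − pe = 0.4608. The values of d and f are assumptions.

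| d | f | Overturn rate | True kappa | Apparent kappa |
|---|---|---|---|---|
| 0.05 | 1 | 5% | 0.89 | 0.89 |
| 0.10 | 0.5 | 5% | 0.78 | 0.89 |
| 0.20 | 0.25 | 5% | 0.57 | 0.89 |
| 0.10 | 0.25 | 2.5% | 0.78 | 0.95 |

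The first three rows would look identical in a correction log, although true kappa runs from 0.57 to 0.89. The log bounds disagreement from below. It cannot identify agreement, because f is unknown.

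**Step 4. What independent readings would give.** Use one shock per patient and a binary classification, with the large-sample standard error of Cohen's kappa (Fleiss-Cohen-Everitt) and equal margins. The simpler form SE = √(po(1 − po)) / ((1 − pe)√n), where po is observed agreement, agrees to about 0.001 in half-width at kappa 0.8. For example, at kappa 0.8, p = 0.50 and n = 90: pe = 0.50, po = 0.50 + 0.8 × 0.50 = 0.90, SE = √(0.90 × 0.10) / (0.50 × √90) = 0.300 / 4.743 = 0.063, and 1.96 × SE = 0.124.

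| Assumed kappa | Prevalence | Half-width, n = 90 | Half-width, n = 50 |
|---|---|---|---|
| 0.8 | 0.25 | 0.144 | 0.194 |
| 0.8 | 0.30 | 0.136 | 0.182 |
| 0.8 | 0.36 | 0.129 | 0.174 |
| 0.8 | 0.50 | 0.124 | 0.166 |
| 0.6 | 0.25 to 0.50 | 0.165 to 0.192 | 0.222 to 0.258 |
| 0.9 | 0.25 to 0.50 | 0.090 to 0.105 | 0.121 to 0.140 |

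The n = 50 column is there because the Discussion says it is not known whether timely access to the recordings is feasible, so 90 readable traces is a best case. The figures apply to ROOR as yes or no. Resulting rhythm has four categories, and its precision will differ.

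**The case against.** **Reliability may mean dependable retrieval.** The Discussion's worked example for ROOR turns on whether timely access to the recording is possible, and where the article means observer agreement it says so, for the mRS tool. On that reading completeness is the right measure. This stands in part: retrieval is one component of reliability and completeness covers it. But the objective is not limited to retrieval, and an outcome that is always retrieved but inconsistently read would not ordinarily be called reliable.

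**A check need not be done with the first reading in view.** The article does not expressly say that the checker sees it. This also stands, so the point rests on the ordinary meaning of the word. The full protocol and analysis plan are not shown and may say more. The point does not rest on their absence, because the article itself fixes both the reading procedure and the outcome measure.

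**ROOR has an explicit rule.** That should help agreement, but it does not show how much agreement is achieved.

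**Stronger readings that the document does not support.**
- A reader might infer that objective 2 cannot be answered. It can be answered in part, since relevance, ease and completeness remain assessable.
- A reader might infer that the rhythm readers know the allocation because the article has "the allocations programmed into the defibrillators by the researcher". That person is not identified as a rhythm reader.
- A reader might take the remark in Blinding that "bias due to unblinding should not be an issue", alongside downloads that show the treatment received, to mean that detection bias will pass into the main trial. POSED plans no formal between-arm comparison of outcomes, and the main trial's reading procedure has not been set.

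**Conclusion.** The point holds in a limited form. Reliability of recording is a stated selection criterion, and for ROOR and resulting rhythm its reader-agreement component is not measured by completeness and cannot be recovered from a perform-then-check reading. The other criteria and the retrieval component are covered. The primary feasibility outcome, the adherence measure and the target of 90 are untouched.

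What is lost is an agreement estimate with a 95% half-width of about 0.12 to 0.14 from 90 traces, or 0.17 to 0.19 from 50. That assumes kappa 0.8, ROOR prevalence of 25 to 50%, one shock per patient and independent readings. It also assumes that the check is made with the first reading visible. If the second reader in fact works independently, only the recording and reporting of agreement need adding. This is a worthwhile, inexpensive improvement and not a flaw that undermines the study.

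**What to change.** 1. Have the existing second reader classify each available first-study-shock trace independently, without sight of the first reading. Where the software allows, hide the displayed energy too, as good practice.
2. Store both readings before any consensus, then resolve differences for the analysis data set.
3. Add inter-reader agreement for ROOR and for resulting rhythm to the secondary feasibility outcomes, reported as percent agreement and kappa with 95% CI, together with the number of traces available.
4. State in the objective that reliability covers both retrieval (completeness) and reading (agreement). If the team intends retrieval only, say so and narrow the objective.

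**Cost.** No extra staff, patients or visits. The second reader's work grows from checking to a full reading of up to about 90 traces, with some effort to hide the energy field. Because traces are read after the event from downloads, the change can be applied to retained recordings even though recruitment has opened.
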